##### Neonatal cerebral magnetic resonance biomarkers

Brain injury score on conventional MRI [19, 20]Proton magnetic resonance spectroscopy thalamic lactate/N-acetylaspartate peak area ratio and absolute concentration of N-acetylaspartate [21]Whole brain maps of diffusion tensor indices [22]

##### Neurodisability (18–22 months)

MortalitySevere neurodevelopmental disability (severe disability was defined as any of the following: a Bayley III [17] cognitive score of < 70; a GMFCS level of 3–5 [18]; blindness; or profound hearing loss (inability to understand commands despite amplification)Microcephaly (head circumference more than 2 standard deviations below the mean)

### Screening and neurological examination

All infants admitted to the neonatal unit with perinatal asphyxia will be screened for eligibility. Out-born babies meeting the inclusion criteria will be eligible for recruitment, irrespective of the temperature at admission to the neonatal unit (Additional file 1). Potentially eligible cases will have a detailed neurological examination by a designated neonatal doctor who is trained and accredited in NICHD neurological examination modified from the Sarnat staging (Table 1) [5]. Briefly, this scoring system assesses six categories of neurological symptoms. The highest score in each category will be recorded. The level of encephalopathy is determined based on the predominant degree of neurological abnormality (moderate or severe) across the six categories. Three out of the total six categories must be moderate or severe for the baby to be eligible.

Infants who have seizures will be considered to have moderate or severe neonatal encephalopathy depending on the neurological examination. Seizures combined with otherwise mild or moderate encephalopathy on neurological examination will be considered as moderate encephalopathy. Seizures combined with severe encephalopathy will be considered as severe encephalopathy. Sedatives or analgesics given before the neurological examination will be recorded in the case report form (CRF).

### Treatment assignment and randomisation

As soon as informed parental consent is obtained for an eligible infant, the recruiting clinician will obtain the treatment assignment, which will be either ‘usual care with cooling’ or ‘usual care only’, using an Internet-based randomisation system (Sealed Envelope; https://www.sealedenvelope.com). Minimisation will be used to ensure balance between the groups with respect to the severity of encephalopathy at each centre. Further details are given in the statistical analysis plan.

Researchers will not be blinded to the intervention (cooling therapy). However, the neurological outcome evaluation at 18 months will be undertaken by assessors masked to the treatment allocation.

### Cooling therapy

Therapeutic hypothermia will be administered using a servo-controlled whole-body cooling device, that has an effective cooling time (percentage of time for which the core body temperature is maintained within the target range of 33 °C to 34 °C) of over 90% [23]. Briefly, this would consist of attaching the mattress to the servo-controlled device, refilling coolant, keeping the baby on the mattress, placing a rectal probe, switching the machine on and selecting the appropriate program. Babies are kept on a radiant warmer with heating turned off and are not clothed, except for nappies. The cooling device will maintain the rectal temperature of the baby within 33 °C to 34 °C and will alarm when temperatures are out of this range (e.g. after displacement of the rectal probe). The clinical team will record rectal temperature hourly in the data collection form. In addition, the temperature data will be downloaded from the cooling device and compared with the manual records to ensure data entry accuracy. After 72 h of cooling, the baby will be automatically re-warmed at 0.5 °C per hour by the cooling device. Following re-warming all babies will have continuous rectal temperature monitoring until 90 h of age, and then every 8 h for the first week after birth.

#### Babies with a low temperature (rectal temperature < 35.5 °C) on admission to the neonatal unit

It is possible that rapid rewarming (>0.5 °C per hour) may result in increased brain injury and seizures. If these babies are already randomised to usual care and then kept under a servo-controlled radiant warmer set at 36.5 °C, rapid re-warming may occur in less than 1 h, thus worsening the outcome.

Hence, any baby admitted with a low rectal temperature (<35.5 °C) who is recruited to the usual care arm will be slowly rewarmed, at a rate not more than 0.5 °C per hour using the protocol below:set the radiant warmer temperature 0.5 °C higher than the baby’s rectal temperature and increase this by 0.5 °C every hour, until the rectal temperature reaches 36.5 °C;if the radiant warmer servo-controlled mode fails, use manual mode keeping the heating output low (e.g. 20%), so that the baby’s rectal temperature does not rise by more than 0.5 °C per hour;if no radiant warmer available, keep the baby covered in warm clothes, so that the temperature slowly increases to 36.5 °C over several hours. This may take as long as 6–12 h.

#### Babies with a core temperature of > 37.5 °C during the first week after birth

All the major neonatal cooling trials to date had up to one-quarter of infants in the usual care having core temperatures > 37.5 °C. Subsequently, analysis of the trial data suggests that core temperatures above 37.5 °C adversely affect brain injury and worsen their outcome [24]. Therefore, any potential benefit seen with cooling may be spuriously related to the overheating of usual care babies. Moreover, a recent trial in adults have shown that ‘therapeutic normothermia’ is as effective as ‘therapeutic hypothermia’ following cardiac arrest [25].

Hence, we will use a more aggressive approach for preventing and treating elevated core temperatures in the usual care arm than the previous neonatal cooling trials. Fever may occur at any time in babies in the usual care arm and sometimes during the post-rewarming phase in the cooling arm. Babies allocated to usual care will be nursed on servo-control radiant warmer with a set temperature of 35.5 °C to 36 °C, to prevent any accidental overheating. Any rise in temperature > 37.5 °C, will be aggressively treated by turning off any radiant heater or warmer if in use, using fans, tepid sponging, antipyretics and, if necessary, using the servo-controlled cooling device in a ‘normothermia mode’. In addition, any infective cause for fever will be investigated and treated, including lumbar puncture if appropriate.

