#### Secondary outcome measures

##### Clinical outcomes (before discharge from hospital)

Mortality from any cause before discharge from hospitalMajor intracranial haemorrhage on cranial ultrasoundGastric bleeds (fresh blood > 5 mL from nasogastric tube)Persistent hypotension (mean blood pressure < 25 mmHg despite maximum inotropic support)Pulmonary haemorrhage (copious bloody secretions with clinical deterioration requiring change(s) in ventilatory management)Persistent pulmonary hypertension (severe hypoxemia disproportionate to the severity of lung disease with a significant pre- and post-ductal saturation difference on pulse oximetry)Prolonged blood coagulation requiring blood productsCulture-proven early onset sepsis (isolation/identification of a pathogenic organism from blood and/or cerebrospinal fluid along with clinical evidence of sepsis and elevation of C-reactive protein)Necrotising enterocolitis (abdominal distension, increased gastric aspirates and/or blood in stools, together with abdominal X-ray showing bowel oedema, pneumatosis or pneumoperitoneum, i.e. Bell’s staging 2 or 3)Cardiac arrhythmia requiring therapySevere thrombocytopenia (<25,000)Persistent metabolic acidosis lasting over 12 h after birthRenal failure (anuria > 48 h with azotaemia)Pneumonia (infiltrates on chest X-ray consistent with infection or aspiration)Subcutaneous fat necrosisNeurological examination at dischargeDuration of hospitalisation

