### Baseline assessments and data collection

The following data points will be recorded in the CRF:maternal (antenatal) and delivery details including resuscitation details;time and date of birth, time of randomisation and start of cooling;birthweight, gestation, gender and head circumference;hourly rectal temperature profile in all infants for the first 90 h;neurological examination within 6 h, at day 3 and at the time of discharge;full blood count (including platelets, CRP and differential white cell count) within 6 h of birth and between days 4 and 7, as a part of clinical care;Blood culture within 6 h of birth and between days 4 and 7;biochemical series (including blood gas, sugar, urea, creatinine, electrolytes and coagulation profile) as a part of clinical care;cranial ultrasound examination (within 72 h) to examine for major intracranial bleeds as a part of clinical care.

Each anonymised CRF will be scanned and emailed to the HELIX trial manager at Imperial College London for quality checks within 48 h of completion. The signed off CRFs will be entered into the HELIX trial database (Redcap®).

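### Culture-proven early onset sepsis can be detected unequally between arms, because cooling suppresses one unscheduled route to a culture: the fever-triggered work-up

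*Protocol article*

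**What the plan says.** All places are in the Methods of the Protocol article.

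- **Trigger.** The section on babies with a core temperature above 37.5 °C during the first week states that "any infective cause for fever will be investigated and treated, including lumbar puncture if appropriate". It applies to both arms.
- **When fever can occur.** The same section says: "Fever may occur at any time in babies in the usual care arm and sometimes during the post-rewarming phase in the cooling arm".
- **Cooling.** Under Cooling therapy: "The cooling device will maintain the rectal temperature of the baby within 33 °C to 34 °C". This lasts 72 h, followed by re-warming at 0.5 °C per hour.
- **Outcome.** Under Clinical outcomes (before discharge from hospital), culture-proven early onset sepsis needs "isolation/identification of a pathogenic organism from blood and/or cerebrospinal fluid along with clinical evidence of sepsis", and also a raised CRP. The definition is not restricted to scheduled samples.
- **Scheduled tests, both arms.** Under Baseline assessments and data collection: "Blood culture within 6 h of birth and between days 4 and 7", and "full blood count (including platelets, CRP and differential white cell count) within 6 h of birth and between days 4 and 7". Screening for perinatal infection adds molecular tests on blood within 6 h of birth. No CSF sample is scheduled.
- **Masking.** Treatment assignment and randomisation says that researchers are not blinded to cooling. Masking is described for the 18-month neurological assessment, the MR analysis and the histopathology, not for in-hospital events.
- **Analysis.** Statistical methods compares categorical secondary outcomes by chi-square or Fisher's exact test, with risk ratios.

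**The concern.** A harm comparison is fair only if the harm is looked for equally hard in both arms. Here the treatment acts on the sign that prompts the search. During cooling a baby can hardly reach 37.5 °C, so a fever-prompted blood culture or lumbar puncture is unlikely; in usual care it can happen on any day. CSF positives count, and the only lumbar puncture the article mentions is the fever-prompted one. Fever may also colour the clinical-evidence element, which staff aware of allocation are likely to judge.

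At stake is the reading of one safety outcome. The Background names co-existent perinatal infection among the reasons why high-income safety data do not carry over. If usual care collects extra positives only because it is cultured more, a modest excess of infection under cooling could be diluted, or equality could be read as benefit.

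**Working it through.** **Plan's own figures.** The article gives no expected sepsis rate and no figure for detection. The only figure needed is the arm size, which reproduces: 50% v 35%, two-sided 5%, 80% power gives 170 per arm, or 183 with continuity correction; 183 / 0.90 = 203.3, so 204 per arm.

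**1. How long the trigger is suppressed.** Assume cooling starts at 2 to 6 h of age (the article fixes only the 6 h limit) and re-warming runs from 33.5 to 36.5 °C.
- Re-warming: (36.5 − 33.5) / 0.5 = 6 h.
- End of re-warming: 2 + 72 + 6 = 80 h, or 6 + 72 + 6 = 84 h.
- Share of the first week (168 h) left: 88 / 168 = 52%, or 84 / 168 = 50%.

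The fever route is open for about half of the first week in the cooled arm and all of it in usual care.

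**2. What the scheduled tests cover.** Samples within 6 h of birth fall around allocation and mainly describe infection already present. The next scheduled culture is on days 4 to 7. Between them, detection depends on clinical prompts, and fever is one of these.

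**3. Possible size with no true effect.** Inputs:
- f, share of usual-care babies febrile: 10% to 25%. The upper end is the article's remark that earlier trials "had up to one-quarter of infants in the usual care having core temperatures > 37.5 °C"; the lower end is assumed.
- y, share of fever work-ups that yield a case: 5% to 20%, assumed.
- r, case rate found by all other routes: 5% to 10%, assumed.
- h, fever yield in the cooled arm relative to usual care: 0.5, assumed from step 1.

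Usual-care rate = r + (1 − r) f y. Cooled rate = r + (1 − r) h f y. Extra cases = 204 × the difference.

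| f | y | r | Usual care | Cooled | Expected RR | Extra usual-care cases |
|---|---|---|---|---|---|---|
| 0.10 | 0.05 | 0.10 | 10.45% | 10.23% | 0.98 | 0.5 |
| 0.175 | 0.125 | 0.075 (midpoints) | 9.52% | 8.51% | 0.89 | 2.1 |
| 0.25 | 0.10 | 0.05 | 7.38% | 6.19% | 0.84 | 2.4 |
| 0.25 | 0.20 | 0.05 | 9.75% | 7.38% | 0.76 | 4.8 |

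Midpoint row: 0.075 + 0.925 × 0.021875 = 0.0952; 0.075 + 0.925 × 0.0109375 = 0.0851; ratio 0.89.

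**4. Compared with sampling error.** For a true RR of 1 with 204 per arm, SE(log RR) = √[2(1/e − 1/204)], where e is the number of events per arm.
- 5% rate: e = 10.2, SE 0.432, 95% interval 0.43 to 2.33.
- 10% rate: e = 20.4, SE 0.297, 95% interval 0.56 to 1.79.

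Every RR in the table lies inside both intervals.

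**The case against.** The strongest answer is that detection is mostly independent of arm. Every baby has cultures and CRP at two scheduled times and molecular screening at the start. The outcome is narrow: early onset, with raised CRP. Fever is not the only prompt, since Supportive care and monitoring leaves additional monitoring to clinical condition and local guidelines. Cooling may increase thrombocytopenia (Adverse events), which could itself prompt cultures in cooled babies, so even the direction is not certain. Fever should be rarer than in earlier trials, because usual-care babies are "nursed on servo-control radiant warmer with a set temperature of 35.5 °C to 36 °C, to prevent any accidental overheating". Tables of unscheduled tests belong in the SAP.

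Most of this stands, and it keeps the point minor. It does not remove it. The early samples cannot show infection arising during cooling, and a baby who dies before the day 4 to 7 culture has no second one. The article gives no age limit for early onset; if the full protocol sets one before day 4, still less of the outcome after allocation rests on scheduled samples. A bias hidden by noise in a sparse comparison still has a direction, and in a safety comparison it can turn a warning into reassurance. The point is not a missing table but an outcome definition that pools positives regardless of why the sample was taken.

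A reader might go further and infer that cooling is bound to look falsely safe. Giving the cooled arm no fever-found cases (h = 0) at f = 25%, y = 10%, r = 5% yields 0.05 / 0.07375 = 0.68, and a true RR of 1.5 would read as 0.075 / 0.07375 = 1.02. The document does not support this. It expects some fever after re-warming in cooled babies, and f is there at its upper end with r at its lower. With h = 0.5 the same inputs give 0.84, and a true 1.5 reads as (0.075 + 0.925 × 0.0125) / 0.07375 = 1.17.

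**Conclusion.** The asymmetry is in the protocol's own text and reaches the sepsis outcome through unscheduled blood cultures, through CSF, and through clinical evidence likely to be judged by unblinded staff. The likely direction favours cooling. The size cannot be derived from the document: work-up yield, base rate and the cooled arm's share of fever-found cases are all assumptions, and the febrile share borrows an upper figure from earlier trials. On those assumptions the expected RR with no true effect is about 0.89 at the midpoints (0.76 to 0.98 over the ranges), or about two extra usual-care cases in 204, well within sampling error. The model also treats fever-found cases as not otherwise detected, which overstates the effect where the day 4 to 7 culture would have found them.

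Severity is minor. One secondary outcome is affected; the primary outcome and the sample size are not.

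**What to change.** Leave clinical care and the defined sepsis outcome as they are. Before unmasking, pre-specify three additions:

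1. A comparison counting only organisms from the protocol-scheduled cultures, with the within-6 h and day 4 to 7 results shown separately. Keep all randomised babies in the denominator, and show deaths before the day 4 to 7 culture by arm.
2. By arm, the number of babies with an unscheduled blood culture or lumbar puncture, the reason, and the positives.
3. A statement that safety for infection will not be concluded from the pooled count alone.

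The scheduled-culture comparison should sit beside the defined outcome, not replace it. Limiting it to babies alive on days 4 to 7 would condition on survival, which cooling may affect (the Background puts newborn-period deaths at about one-third), and using it alone would set aside genuine early cases.

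The cost is one extra table and few events in the scheduled-only analysis. No new samples are needed.

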### Criteria for stopping cooling therapy

Refractory hypotension (mean blood pressure < 25 mmHg) despite optimal inotropic and volume supportLife-threatening/massive haemorrhageParent or clinician request to stop cooling therapy, for example if the baby requires any surgical procedure during first three days

### Supportive care and monitoring

The general management of babies will be standardised at the participating centres and will not permit therapies like steroids, mannitol or other experimental therapies in recruited infants.

Hourly vital signs (oxygen saturation, heart rate, non-invasive blood pressure, rectal temperature) will be recorded in the HELIX CRF in all infants. Additional monitoring will be dictated by the clinical condition and local guidelines.

Infants may also receive intravenous fluids, antibiotics, ventilatory support, inotropes, blood products, sedation, muscle relaxants and anti-convulsants as per the local clinical practice. The babies undergoing cooling therapy will also receive sedation, if they are ventilated or if there is any evidence of stress (for example, shivering, unexplained tachycardia).

Detailed neurological examination (using NICHD criteria) will be performed within 6 h of birth, then at day 3 and at discharge from hospital.

### Baseline assessments and data collection

The following data points will be recorded in the CRF:maternal (antenatal) and delivery details including resuscitation details;time and date of birth, time of randomisation and start of cooling;birthweight, gestation, gender and head circumference;hourly rectal temperature profile in all infants for the first 90 h;neurological examination within 6 h, at day 3 and at the time of discharge;full blood count (including platelets, CRP and differential white cell count) within 6 h of birth and between days 4 and 7, as a part of clinical care;Blood culture within 6 h of birth and between days 4 and 7;biochemical series (including blood gas, sugar, urea, creatinine, electrolytes and coagulation profile) as a part of clinical care;cranial ultrasound examination (within 72 h) to examine for major intracranial bleeds as a part of clinical care.

Each anonymised CRF will be scanned and emailed to the HELIX trial manager at Imperial College London for quality checks within 48 h of completion. The signed off CRFs will be entered into the HELIX trial database (Redcap®).

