### Aims

#### Primary

To examine whether whole-body cooling to 33.5 °C, initiated within 6 h of birth and continued for 72 h, reduces death or moderate or severe neurodisability at 18–22 months after neonatal encephalopathy, in LMICs.

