### Adverse events

All known adverse events relating to neonatal encephalopathy and cooling therapy are described in the parent information leaflet and will be part of obtaining the informed research consent, before the start of cooling therapy.

The following clinical events (1–9) occur due to the underlying disease (neonatal encephalopathy). Cooling trials from high-income countries have shown that cooling therapy reduces/does not increase the incidence of many of these clinical events in encephalopathic babies.Death during neonatal period or during infancyBrain injury observed with MRIAdverse neurodevelopmental outcome at 18 months and at childhoodPersistent pulmonary hypertensionMetabolic imbalancesCardiac arrhythmiaRenal failureCoagulopathyGastric bleeds

Cooling therapy may increase the risk of the following adverse events noted in the previous randomised controlled trials.Thrombocytopenia and increased need for platelet transfusionsSubcutaneous fat necrosis

All adverse events are expected to occur within the cooling period (first 72 h) or within 72 h of re-warming. Adverse reactions occurring subsequently (after one week of life), except subcutaneous fat necrosis, will not be considered as intervention related. Subcutaneous fat necrosis may occur several weeks after the therapy.

If an unexpected serious adverse event (SAE) occurs (i.e. an event not mentioned in the above list), it should be reported to the HELIX trial manager within 24 h, using one of the SAE report forms. The HELIX trial manager will ensure that the independent data monitoring committee (IDMC) and the research ethics committee (REC) are informed accordingly.

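### Platelet transfusion, part of a harm the protocol says cooling may increase, is not an outcome, and no platelet count is scheduled between about 6 h of age and day 4

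*Protocol article*

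**What the plan says.** The Adverse events section of the protocol article separates events due to the encephalopathy from those that cooling may cause. The second list opens with "Cooling therapy may increase the risk of the following adverse events noted in the previous randomised controlled trials" and has two entries: low platelets together with a greater need for platelet transfusion, and subcutaneous fat necrosis. The same section gives the period at risk: "All adverse events are expected to occur within the cooling period (first 72 h) or within 72 h of re-warming".

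Among the 17 clinical outcomes before discharge (Secondary outcome measures), the only platelet outcome is severe thrombocytopenia, set at a count below 25,000. Blood products appear only within an outcome for prolonged coagulation. Platelet transfusion is not listed.

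Baseline assessments and data collection asks for a "full blood count (including platelets, CRP and differential white cell count) within 6 h of birth and between days 4 and 7", and adds that these counts belong to routine care. The primary aim describes cooling as "initiated within 6 h of birth and continued for 72 h", and Cooling therapy adds: "After 72 h of cooling, the baby will be automatically re-warmed at 0.5 °C per hour by the cooling device".

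Under Supportive care and monitoring, babies may receive "blood products, sedation, muscle relaxants and anti-convulsants as per the local clinical practice", and "Additional monitoring will be dictated by the clinical condition and local guidelines". Treatment assignment and randomisation states that those running the trial are not masked to cooling. The expedited reporting rule begins "If an unexpected serious adverse event (SAE) occurs (i.e. an event not mentioned in the above list", so it does not extend to the two listed harms.

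**The concern.** The article names a harm in two parts, low platelets and the transfusions given for them, but fixes an outcome for the severe end of the first part only. Transfusion is both a component of the named harm and a treatment that can keep a baby from reaching the cut-off that defines the outcome. The interval in which no count is fixed covers most of the exposure, so low counts arising then are seen only if someone chooses to test. Those who choose know the allocation and follow local habits. At stake is whether the trial can measure, and compare fairly between arms, one of the two risks it says cooling may add.

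**Working it through.** The article gives no rate for low platelets or platelet transfusion, so there is no figure of the plan to reproduce on this point. The check is a timeline, a reading of the definitions, and an illustration on assumed rates.

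**Timeline (hours of age)**

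- Cooling starts between 0 and 6 h and lasts 72 h, so it ends between 72 and 78 h.
- Rewarming from 33.5 °C to 36.5 °C (end point assumed for this calculation) at 0.5 °C per hour takes 3.0 / 0.5 = 6 h, so it ends between 78 and 84 h.
- Adding 72 h after the end of rewarming, the stated risk period closes between 150 and 156 h.
- The first scheduled count, at or before 6 h, is in effect a baseline value.
- If days are 24-hour periods and the first is day 1, day 4 begins at 72 h. If the first is day 0, it begins at 96 h. Counting by calendar date could bring day 4 somewhat earlier for a baby born late in the day.
- The interval without a scheduled count is therefore at least 72 − 6 = 66 h under the first convention, or 96 − 6 = 90 h under the second. At least 66 of the 72 h of cooling lie inside it.
- A baby who dies before day 4 has no scheduled count after baseline.

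**What happens to one baby.** Take a baby whose platelets fall during cooling, with no bleeding and no prolonged coagulation, and who is given platelets at a count of 25,000 or above.

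- The platelet outcome is not met.
- The coagulation outcome is not met.
- The expedited reporting rule does not apply, because the event is on the list.
- The scheduled count on days 4 to 7 may be a post-transfusion value.

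This follows even if the plan is carried out exactly as written.

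**Direction of bias (all rates assumed).** In the first three rows, 20% of cooled and 10% of usual-care babies would fall below 25,000 if never transfused (true RR 2.0), and the shares are those transfused first. In the last row the true rate is 10% in both arms, and the shares are those whose low count is detected.

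| Assumption | Cooled | Usual care | Observed RR |
|---|---|---|---|
| 60% transfused first in both arms | 20% × 0.4 = 8% | 10% × 0.4 = 4% | 2.0 |
| 60% cooled, 20% usual care transfused first | 20% × 0.4 = 8% | 10% × 0.8 = 8% | 1.0 |
| 20% cooled, 60% usual care transfused first | 20% × 0.8 = 16% | 10% × 0.4 = 4% | 4.0 |
| No true difference; 60% cooled, 20% usual care detected | 10% × 0.6 = 6% | 10% × 0.2 = 2% | 3.0 |

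**Loss of information without bias (rates assumed).** Let the harm be a count below 25,000 or a platelet transfusion, captured equally in both arms. The plan's number per arm is 183 / (1 − 0.10) = 203.3, rounded up to 204. All 204 are used because these are in-hospital outcomes. With p̄ the mean of the two rates, two-sided 5%:

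power = Φ{ [ |p1 − p2| − 1.96 √(2p̄(1 − p̄)/n) ] / √[ (p1(1 − p1) + p2(1 − p2))/n ] }

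For 10% v 20%: (0.100 − 1.96 × 0.03536) / 0.03501 = 0.88, so power is 81%.

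| Usual-care rate, RR 2 | All captured | Half captured | A quarter captured |
|---|---|---|---|
| 5% | 48% | 26% | 15% |
| 10% | 81% | 48% | 26% |
| 20% | 99% | 81% | 48% |

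At a 10% usual-care rate, the observed excess falls from about 20 babies to 10 to 5.

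**The case against.** The strongest reply has several parts.

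- **The two counts are a recording minimum.** They are described as part of routine care, and the outcome list covers the whole stay before discharge. On a plain reading, a count below 25,000 on any clinical sample qualifies. This stands: it would be wrong to say that the outcome rests on two samples only.
- **The later count lies within the risk period.** That period runs to about 150 to 156 h, so a count on days 4 to 7 can fall inside it. This stands. It does not fill the interval during cooling, and it does not undo an earlier transfusion.
- **Other outcomes catch some of these babies.** Intracranial, gastric and pulmonary bleeding and prolonged coagulation are all counted. This stands, and it limits the gap to isolated low platelets treated at 25,000 or above.
- **A laboratory cut-off is more objective than a decision to transfuse.** This stands, and it argues against merging the two. It does not argue against reporting transfusion separately.
- **Material is not shown.** The assessment schedule figure, the case report form and the monitoring committee's report format may hold transfusion data. That is possible, but recording an item does not make it one of the outcomes compared between arms, and the article's outcome list omits it.

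A reader might infer more: that treating the harm hides it, so that the arms will look alike or cooling will look safer. The documents do not support this. Readier transfusion of cooled babies would hide harm, but readier testing of cooled babies would exaggerate it, and nothing in the article shows which would dominate or that practice differs by arm at all.

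**Conclusion.** The point holds in a limited form. The platelet outcome covers only part of a harm that the article itself names, and no count is scheduled for at least 66 of the 72 h of cooling if day 4 begins at 72 h of age. A baby with an isolated low count who is transfused at 25,000 or above is not an event on that outcome. Such a baby is not necessarily absent from every safety outcome, so it would go too far to say that the trial counts all of them as unharmed.

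Ascertainment may differ between arms, in either direction and to an unknown extent. The illustrative risk ratios (1.0 to 4.0 around a true 2.0, and 3.0 where there is no true difference) and the power figures rest entirely on assumed rates. They show what could happen and are not estimates. The primary endpoint and the sample size are unaffected.

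**What to change.** - Keep a platelet count below 25,000 as its own outcome, and state that it applies to any sample before discharge.
- Add any platelet transfusion from randomisation to discharge as a separate secondary safety outcome, compared by arm.
- Report by arm the lowest recorded platelet count and the number of platelet counts per baby, so that unequal testing can be seen.

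The cost is a line in the outcome list and a few data fields filled from clinical records, if the case report form does not already hold them. No extra blood sample is needed and transfusion practice does not change. The small downside is that transfusion reflects decisions by unblinded staff, which is why it should stand beside the laboratory outcome and not be merged with it.
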